### Study objectives

Despite advancements in MST and ECT for MDD, there remains a need for further research to replicate clinical outcomes and understand the therapeutic targets of these treatments. This project titled “Chinese Union: Replication, Efficacy, and Safety of Seizure Therapy with Evaluation-based Precision (CURES-STEP)” phase I initiated by the [removed for peer review], aims to address these gaps through a double-blinded, randomized, non-inferiority investigation comparing the efficacy, tolerability, cognitive adverse effects, and neurophysiological biomarkers of MST and bilateral ECT in patients with MDD. The primary objectives of the study are twofold: 1. To replicate the comparable antidepressant efficacy and reduced side effects (with HVLT-R as an additional primary outcome) observed in previous comparisons between MST and ECT. 2. To utilize electroencephalography (EEG) (25) and electrocardiography (ECG) (23) markers as neurophysiological biomarkers to assist in treatment decision-making between ECT and MST, and to predict treatment outcomes including antidepressant effects and cognitive side effects. We believe that MST and ECT are not simply interchangeable treatments, and that leveraging neurophysiological characteristics may help tailor treatment decisions for individual patients with MDD. By examining both clinical outcomes and neurophysiological biomarkers, we aim to provide valuable insights into the efficacy, safety, and personalized treatment approaches for MDD using seizure therapies. Additionally, this study aims to validate the clinical application value of a domestically developed MST device approved by the National Medical Products Administration (NMPA) in China, as previous MST studies utilized the MagPro MST (MagVenture A/S, Denmark) device (26, 27).

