### Study design

The present clinical protocol is designed as a double-blind, parallel, non-inferiority, randomized clinical trial.

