### Assessments

#### Clinical measures

Clinical assessments will be administered by blinded raters at various time points throughout the study, including baseline, post-session 3, 6, 9, and 12 (3 hours after each session), as well as at the 4-week, 8-week, and 12-week follow-up visits. The primary outcome measure was the total score on the 24-item Hamilton Depression Rating Scale (HDRS-24) (28). Additionally, the Hamilton Anxiety Scale (HAMA) (30), clinician-rated, served as a secondary outcome measure. Other assessments included self-reported measures such as the Self-Rating Depression Scale (SDS) (31) and the Self-Rating Anxiety Scale (SAS) (32), as well as clinician-rated measures including the Global Assessment of Functioning (GAF) scale (33). Follow-up assessments were conducted monthly. Prior to the commencement of the experiment, all subjects will undergo an interview using the MINI-International Neuropsychiatric Interview (M.I.N.I. 5.0) (34). Additionally, participants filled out a self-administered questionnaire to provide demographic information.

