### Outcomes

#### Primary outcome

The primary outcome measure is the change in HDRS-24 total score from baseline to the 12-week follow-up, which is assessed after the completion of the 12-session acute treatment phase (conducted over 4 weeks) and a subsequent 12-week post-treatment observation period. A reduction of at least 50% in the HDRS-24 score indicated a response to treatment, while a reduction of at least 60% in the HDRS-24 score and a total score of 8 or less indicated remission. Change in HVLT-R total recall score from baseline to the 12-week follow-up (assessing verbal memory, a key cognitive domain sensitive to seizure therapy effects).

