## Data entry and analyses

This trial aims to provide replicated evidence that MST is as effective as ECT in terms of remission rates, response rates, and reduction of depressive symptoms (assessed by the primary outcome: change in HDRS-24 from baseline to 12-week follow-up after the acute treatment phase) and superior in preserving verbal memory (via HVLT-R as an additional primary outcome), with fewer physical and cognitive side effects overall. Additionally, this study will explore personalized electrophysiological indicators (EEG/ECG) in an exploratory manner to inform future individualized treatment decisions for ECT and MST, and to generate hypotheses about the physiological mechanisms underlying the antidepressant efficacy and cognitive effects of MST/ECT. To our knowledge, this will be the largest RCT comparing ECT and MST in China. The trial will provide evidence to determine whether individualized treatment decisions based on personalized electrophysiological characteristics hold promise for optimizing the balance between efficacy and side effects (40). Specifically, it will offer insights into the potential effect sizes, acceptability, feasibility, and safety of the novel interventions under investigation. Predicting efficacy and side effects based on physiological characteristics, such as indicating greater side effects with ECT and comparable efficacy but fewer side effects with MST for patients with MDD, suggests that MST may be more suitable for these patients. Alternatively, physiological characteristics indicating superior efficacy with ECT compared to MST, with comparable side effects between the two, suggest that ECT may be more appropriate for these patients.

Firstly, data entry will undergo a thorough double-check to ensure accuracy. Data quality will then be assessed, with particular attention given to data distribution, and outliers will be excluded from subsequent analysis. Once data integrity is confirmed, detailed analyses of primary and secondary outcomes will be conducted using IBM SPSS Statistics 20 for Windows (Armonk, NY: IBM Corp).

Descriptive statistics, such as mean and standard deviation, will be computed for each study arm separately. Analyses will be performed within the intention-to-treat (ITT) framework to assess the effectiveness of interventions for all participants, utilizing multiple imputed datasets to address missing data.

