Appropriate statistical methods will be employed for data analysis, including mixed-effects models for repeated measures (MMRM). MMRM with a factorial design (3 time points × 2 conditions) will be conducted to examine significant interactions between time (baseline, Day 30, and Week 12) and condition (ECT and MST), while adjusting for potential covariates such as age, sex, duration of illness, age of onset, IQ, and antidepressant usage. This approach is robust to missing data under the missing-at-random (MAR) assumption and provides unbiased estimates of treatment effects. The significance level will be set at 0.05.

Sensitivity analyses will be performed to assess the robustness of results to missing data, including multiple imputation (MI) under MAR and missing-not-at-random (MNAR) assumptions. Results from MMRM and MI will be compared. Exploratory analyses will include subgroup analyses by demographic/clinical characteristics and correlation analyses between neurophysiological biomarkers (EEG/ECG) and treatment outcomes, using linear or logistic regression models as appropriate.

Subgroup analyses will compare relapse rates and time-to-relapse between participants who received maintenance treatments versus those who did not, within both MST and ECT groups. This will help disentangle the effects of acute treatment from post-treatment management strategies.

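### Two primary outcomes share one undivided 0.05 level, and the article does not say how they combine into a primary conclusion

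*Protocol article*

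**What the plan says.** **First primary outcome.** The Primary outcome section states: "The primary outcome measure is the change in HDRS-24 total score from baseline to the 12-week follow-up". Under Study design the trial is "designed as a double-blind, parallel, non-inferiority, randomized clinical trial", so the HDRS-24 question is one of non-inferiority.

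**Second primary outcome.** The same section then lists "Change in HVLT-R total recall score from baseline to the 12-week follow-up". Study objectives refers to "reduced side effects (with HVLT-R as an additional primary outcome", and Data entry and analyses says MST is expected to be "superior in preserving verbal memory (via HVLT-R as an additional primary outcome". The HVLT-R question is therefore one of superiority.

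**Error rate and analysis.** Data entry and analyses gives one sentence on the level: "The significance level will be set at 0.05". It does not give sidedness or assign the level to an outcome. The analysis described is "MMRM with a factorial design (3 time points × 2 conditions) will be conducted to examine significant interactions".

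**Sample size.** Sample size estimation and Figure 2 describe a single calculation for one test at alpha 0.05 with power 0.95. It gives 166 participants, raised to 210 for 20% dropout.

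**The concern.** The two primary outcomes carry different hypotheses, and the text does not determine which result, or which combination, decides the trial. One undivided level and a sample size for one test would suit a trial with a single primary test.

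The gap matters most when the results disagree. Suppose HDRS-24 non-inferiority is not shown but HVLT-R favours MST. Nothing in the article prevents the memory result from being reported as a primary success, although the design is built around non-inferior antidepressant effect. A rule chosen after the results are seen would not protect the error rate.

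**Working it through.** **1. The article's own figure.** Inputs from Sample size estimation and Figure 2: f = 0.1, alpha = 0.05, 2 groups, 6 measurements, correlation 0.5, epsilon 1.

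- λ = f² × N × m / (1 − ρ) = 0.01 × 166 × 6 / 0.5 = 19.92
- df = (2 − 1)(6 − 1) = 5 and (166 − 2)(6 − 1) = 820
- Critical F = 2.22502; power = 0.9501 (N = 164 gives 0.947)
- 166 / 0.8 = 207.5, so 208, or 210 as 7 centres × 30

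The figure reproduces, and it is for one test at one undivided 0.05.

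**2. Error rate if either outcome may carry a primary claim.** The assumptions are mine, because the article does not give them:

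- Both nulls are true: MST is worse on HDRS-24 by the margin, and HVLT-R does not differ.
- Each test is valid at its level.
- The two tests are independent.

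The chance of at least one false claim is 1 − (1 − α₁)(1 − α₂).

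| Reading of the level | Calculation | Result |
|---|---|---|
| Both tests two-sided at 0.05 | 1 − 0.95 × 0.95 | 9.75% |
| One test at 0.05, the other at 0.025 | 1 − 0.95 × 0.975 | 7.4% |
| Only claims favouring MST, 0.025 each | 1 − 0.975 × 0.975 | 4.9%, against a nominal 2.5% |

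**3. Correlation between the two test statistics.** The article gives no value, so a range is shown, from the bivariate normal distribution.

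| r | Two-sided, 0.05 each | Favouring MST, 0.025 each |
|---|---|---|
| 0 | 9.75% | 4.94% |
| 0.3 | 9.51% | 4.76% |
| 0.5 | 9.07% | 4.54% |
| 0.7 | 8.35% | 4.17% |
| 0.9 | 7.04% | 3.52% |

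**4. Error rate if both must succeed.** A false joint claim requires rejecting at least one true null, and both tests must reject. Its probability cannot exceed the larger single-test level, so there is no inflation. The cost falls on power. If each test had power 0.95 and they were independent, joint power would be 0.95 × 0.95 = 0.9025.

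**5. What each remedy costs on the article's G\*Power inputs.**

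- *Equal split, 0.025 each.* Error is 4.94% if independent. The required N rises from 166 to 190, and 190 / 0.8 = 237.5, so 238 after dropout. At the planned 210, 210 × 0.8 = 168 remain, and power per outcome is about 0.92.
- *Fixed sequence, HDRS-24 first.* If the HDRS-24 null is true, any false primary claim requires a false first step, so the rate is at most 0.025. If MST is truly non-inferior, the only possible false claim is on HVLT-R, at most 0.05 two-sided. No split of alpha is needed.

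**The case against.** **A multiplicity rule usually sits in the analysis plan.** That plan is not shown, and a journal article condenses. This stands as far as it goes: the absence of a detailed procedure would not be a finding. What remains is that the article itself fixes two primary outcomes with different hypotheses, one undivided level and a sample size for one test. Those statements leave the primary conclusion undetermined.

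**The aim is conjunctive.** Data entry and analyses joins equal effectiveness and better verbal memory with an *and*. Read as a success criterion, that removes the inflation. But the sentence is an aim and not a decision rule, and it also takes in response, remission and physical side effects.

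**A reader might infer that each outcome is tested at 0.05, that either success counts, and so that the error rate is nearly double the stated level.** The article does not support this as fact. No sentence sets the level per outcome or allows an either/or claim. The 9.75% also counts rejections in both directions, whereas the claims of interest run one way. For those the figure is 4.9%, which is nearly double only against a 2.5% reference that the article does not state.

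**A reader might also see a contradiction in Clinical measures**, which says: "The primary outcome measure was the total score on the 24-item Hamilton Depression Rating Scale". The text does not bear this out. Cognitive assessments names HVLT-R as the primary outcome of the cognitive battery, so each section names the primary for its own domain.

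**The arithmetic presumes a valid HDRS-24 non-inferiority test.** This stands. The article describes an interaction test and states no margin. If non-inferiority were read from a non-significant interaction, its false-claim rate would not be held at 0.05, and the figures above would not apply to it.

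**Conclusion.** The point holds in conditional form: the article sets up two primary outcomes and does not say how they combine.

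The size depends on the rule. With an either/or claim, both nulls true and independent tests, it is 9.75%, 7.4%, or 4.9% against 2.5%, according to sidedness and levels. It is lower with correlation. If both outcomes must succeed, there is no inflation. Where MST is truly non-inferior on HDRS-24, only the HVLT-R claim can be false, and its error is its own level.

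It should not be reported as an established doubling of the error rate. It is worth correcting because the remedy is close to free and must be set before results are known. The article gives December 2027 as the end of the trial.

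**What to change.** In Data entry and analyses, state one of two rules.

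1. **Fixed sequence (preferred).** First test HDRS-24 non-inferiority, as the between-group contrast in change at Week 12 against a prespecified margin, at one-sided 0.025. Only if it succeeds, test HVLT-R superiority at two-sided 0.05.
2. **Both must succeed.** If the joint aim is meant as the success criterion, say that the trial succeeds only if HDRS-24 non-inferiority and HVLT-R superiority are both shown.

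The rule itself takes two sentences. The first step also needs the margin and the Week 12 contrast, which the article does not state. If the full protocol or analysis plan holds them, the article need only give them.

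The fixed sequence does not split alpha, so the multiplicity rule adds no patients. Its small downside is that HVLT-R cannot be claimed as a primary success if HDRS-24 non-inferiority fails; the result could still be reported as supportive. The both-must-succeed rule also leaves alpha whole, but the power to plan for is then the joint power.

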#### EEG acquisition

Participants will be seated in a dimly lit, sound-attenuated, and electrically shielded room for EEG data collection. EEG data will be recorded using a 64-channel electrode cap (Brain Products Inc., Bavaria, Germany). Electrodes for electrooculography (EOG) will be positioned below the left eye and above the right eyebrow. Bilateral mastoids will be utilized as reference electrodes, with AFz serving as the ground electrode. EEG signals will be digitized at a sampling rate of 1000 Hz and bandpass filtered between 0.016 and 200 Hz using filters from Brain Products Inc. Electrode impedance will be maintained below 5 kΩ throughout EEG data collection. Participants will be instructed to sit comfortably with their eyes closed for 5 minutes and then with their eyes open for another 5 minutes.

Offline preprocessing and subsequent analysis of resting state EEG (rsEEG) data will be conducted using EEGLAB (36) and MATLAB (MathWorks, Natick, Massachusetts). The EEG data preprocessing pipeline will involve several steps to ensure data quality and prepare it for analysis. This included bandpass filtering between 0.5 and 70 Hz with notch filtering at 50 Hz, downsampling to 512 Hz, and visual inspection to remove epochs with severe artifacts. Independent component analysis (ICA) will be used to remove blink and horizontal eye movement artifacts, followed by interpolation of bad channels and re-referencing to the average reference. Subsequently, artifact-free segments of 60 seconds will be selected for power spectral density estimation using Welch’s method with a Hamming window of 2 seconds and 50% overlap between segments, resulting in a frequency resolution of 0.5 Hz (37). Absolute power values will be calculated for predefined frequency bands, including delta (1–4 Hz), theta (4–8 Hz), alpha1 (8–10 Hz), alpha2 (10-12.5 Hz), beta1 (12.5-18.5 Hz), and beta2 (18.5–30 Hz). Additionally, relative power will be computed as the proportion of power within each specific frequency band relative to the total power across all frequency bands. Analyses of EEG data are exploratory and aimed at identifying potential associations with treatment outcomes.

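### Choosing between ECT and MST from EEG/ECG markers is part of a primary objective, but the stated marker-outcome correlations do not test whether the treatment difference varies with the marker

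*Protocol article*

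**What the plan says.** The Study objectives section of the protocol article states: "The primary objectives of the study are twofold". The second objective is to use EEG and ECG "markers as neurophysiological biomarkers to assist in treatment decision-making between ECT and MST, and to predict treatment outcomes including antidepressant effects and cognitive side effects". It therefore has two parts: choosing a treatment, and predicting outcome.

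The opening of Data entry and analyses describes the inference wanted. Some physiological profiles would point to MST as the more suitable treatment. Others, "physiological characteristics indicating superior efficacy with ECT compared to MST", would point to ECT.

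The same section then states one marker analysis: "correlation analyses between neurophysiological biomarkers (EEG/ECG) and treatment outcomes, using linear or logistic regression models as appropriate". The only interaction it names is time by condition, which contains no marker. On subgroups it says "Exploratory analyses will include subgroup analyses by demographic/clinical characteristics"; EEG and ECG markers are not listed as subgroup factors.

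On status, the EEG acquisition section says "Analyses of EEG data are exploratory". The ECG acquisition section says the same of the HRV indices, and Data entry and analyses describes the electrophysiological work as exploratory and hypothesis-generating.

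**The concern.** A marker helps choose between two treatments only if the difference between them changes with the marker. That is a treatment-by-marker interaction. A marker-outcome association answers a different question: who does well, whatever the treatment. A marker that predicts improvement equally under ECT and MST has a strong association with outcome and no bearing on the choice.

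The trial can address the treatment-choice question, because allocation is randomised 1:1 and EEG and ECG are recorded at baseline in both arms. The gap lies in the analysis named for that aim. If the stated correlations were read as evidence for treatment choice, prognostic markers could be mistaken for selective ones.

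There is also a conflict of labels. The aim is primary in Study objectives and exploratory in the sections that describe its analysis.

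**Working it through.** **Numbers available.** The Figure 2 legend gives f = 0.1, 2 groups, 6 measurements, correlation 0.5 and total N = 166. This reproduces:

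- λ = N × m × f² / (1 − ρ) = 166 × 6 × 0.01 / 0.5 = 19.92
- df = 5 and (166 − 2) × 5 = 820; power 0.950
- 166 / 0.80 = 207.5, so 208; seven centres of 30 give 210

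This sample size is for time by group and involves no marker. With the 20% dropout allowed for, 210 × 0.80 = 168 patients, or 84 per arm. That N is used below.

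**Assumptions.** The protocol gives no marker effect sizes, so the slopes are assumed: standard normal marker, outcome variance about 1, one marker, two-sided 0.05.

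**Formulas (normal approximation).**

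- Correlation: power ≈ Φ(atanh(r) × √(n − 3) − 1.96)
- Slope difference d between arms: SE ≈ √(4/168) = 0.154; power ≈ Φ(d / 0.154 − 1.96)

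**Case 1, purely prognostic marker (0.3 in both arms).**

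- Pooled: atanh(0.3) × √165 = 3.98, so power is 0.98.
- Per arm: atanh(0.3) × √81 = 2.79, so power is 0.80 in each arm. The chance of significance in exactly one arm is 2 × 0.80 × 0.20 = 0.32; simulation gives about 31%.
- Interaction test: the true difference is zero, so it rejects at the nominal 5%.

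**Case 2, opposite slopes (+0.3 and −0.3).**

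- Pooled: the slopes cancel, and about 6% of simulated trials reject.
- Interaction: d = 0.6 and 0.6 / 0.154 = 3.89, so power is 0.97; simulation gives 97% to 98%.

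**Case 3, marker acting in one arm only (0 and 0.4).**

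- Pooled: the average slope is 0.2; atanh(0.2) × √165 = 2.60, so power is 0.74.
- Interaction: d = 0.4 and 0.4 / 0.154 = 2.59, so power is 0.74. In simulation both tests come to about 75%.

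| Assumed slopes | Pooled correlation | Interaction test |
|---|---|---|
| 0.3, 0.3 | 98% | 5% |
| −0.3, +0.3 | 6% | 98% |
| 0, 0.4 | about 75% | about 75% |

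In case 3 the pooled test detects the marker as often as the interaction test does, but a positive pooled result looks the same as one from case 1.

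**What the interaction test can detect.** At 80% power, (1.96 + 0.84) × √(4/168) = 0.43. At N = 210 it is 0.39.

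**Number of tests.** Six EEG bands as absolute and relative power give 12. Heart rate plus 14 HRV indices give 15. That is 27 markers. With the two primary outcomes, HDRS-24 and HVLT-R, there are 54 tests. If every marker were null, 54 × 0.05 = 2.7 would be significant by chance, before channels or time points are counted.

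**The case against.** The strongest reply is that the text does not say the correlations are pooled. A linear or logistic regression can hold an arm-by-marker term, and the list of exploratory analyses is not presented as exhaustive. Run within each arm, the correlations would pick up the opposite-slope marker in at least one arm in about 96% of trials. This stands against one tempting inference, that the plan would miss selective markers. That holds only for pooled correlations with near-symmetric opposite slopes, and case 3 shows it is not general. The reply does not rescue the plan. Per-arm testing does not compare the arms, and significance in one arm only arises in about 31% of trials for a marker with identical slopes.

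Second, a condensed article may leave model terms to a fuller document. That is fair for detail. Here, though, the article states both the aim and the analysis, and the two do not match.

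Third, the correlations do serve the prediction part of objective 2, so they should stay for that purpose.

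Fourth, the work is described as exploratory, to inform future decisions and generate hypotheses. A reader might infer that the results will be issued as treatment guidance; the wording does not support that. The exploratory label lowers the stakes, but an exploratory analysis should still address its own question, and the label conflicts with the primary status given in Study objectives.

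**Conclusion.** The concern holds for the treatment-choice part of objective 2. The stated analysis addresses prediction and, pooled or per arm, does not test whether the MST-ECT difference varies with a marker. The practical risk is that prognostic and selective markers cannot be told apart. How often this would mislead depends on slopes the protocol does not give: the 98%, 31% and 6% figures are illustrations under assumed slopes at N = 168, one marker at a time. The label conflict on objective 2 needs no assumption; it is in the text. The point deserves correction but does not touch the main efficacy comparison.

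**What to change.** In Data entry and analyses, for the treatment-choice aim, regress Week-12 change on arm, baseline marker, arm × baseline marker and baseline score. Report the interaction estimate with its confidence interval. Across the listed markers, either control the false discovery rate or label the results clearly as hypothesis-generating. Keep the marker-outcome correlations for the outcome-prediction aim only.

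In Study objectives, relabel objective 2 as exploratory, in line with the EEG, ECG and analysis sections.

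This changes wording only. Baseline EEG and ECG in both arms are already planned, so no extra data are needed. The price is modest power: a slope difference of about 0.43 is needed for 80% power at N = 168, before any multiplicity control, so fewer markers will be flagged.
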